### Data Collection

In-depth interviews will be audio-recorded, and notes will be taken by the field investigators and research assistants. Qualitative data from in-depth interviews will be transcribed verbatim, translated into English, and imported into MAXQDA (version 2020; VERBI Software) for analysis.

The data collection and management of cultural epidemiology will be done using the Open Data Kit (ODK) tool (GetODK). Data will be collected digitally on an Android tablet using the ODK Collect application. Later, the data will be uploaded to a cloud server. From there, the data set will be downloaded as an Excel (Microsoft Corp) spreadsheet.

### Data Security

All interviews will be recorded for documentation. The information recorded is confidential. Data sheets, audio records, and transcripts will have unique identifier codes. They will not bear the participant’s name. Soft copies (ie, audio records and transcripts) will be stored electronically on password-protected external hard disks or drives. Hard copies (ie, data sheets) will be stored under lock and key at the faculty office. Informed consent forms will bear participants’ names and signatures. Therefore, they will be kept under lock and key separately from data sheets, audio records, and transcripts. They will be accessible through only the principal investigator or coinvestigators, with lists linking unique identifier codes to names. Data sheets, audio records, transcripts, and informed consent forms will be destroyed (by incineration or digital erasure) 3 years after study completion.

### Analysis Plan

The primary goal of the study is to clarify descriptive, comparative, and analytic accounts of explanatory models of COVID-19 and how they explain awareness, acceptance, and use of vaccines. Comparative analysis will focus on questions of gender and rural-urban features of the COVID-19 pandemic and determinants of anticipated acceptance or refusal of COVID-19 vaccines.

### Qualitative Analysis

The in-depth interviews of community members will provide their views on the risk of contracting the virus, behavior to prevent the virus, experience and meaning of COVID-19, and their perception of COVID-19 vaccination. The interviews with health care workers will provide their views about COVID-19 vaccine priorities and practices and their recommendations for promoting the rollout of vaccination. All these in-depth interviews will be transcribed verbatim, verified against the audio tapes, and translated into English. The English transcripts will then be imported into MAXQDA software for managing the data. Thematic analysis will be used as an inductive and deductive process. Analysis involves familiarization with the data, generation of codes, and discovery of initial themes. Themes will be refined through an interactive process, and a coding framework will be developed that reflects the core themes [23]. A team of research assistants with author ES will develop codes using an inductive approach, allowing themes to emerge from the data. A coding framework will be used to categorize codes and identify meaningful and potential themes. We will perform peer debriefing regularly to discuss the emerging themes and interpretations, ensuring the rigor of the analysis.

### Quantitative Analysis

The epidemiological survey will be conducted on tablets with ODK software. All interviews will be uploaded electronically to Google Spreadsheets (Google Inc). The final data set will be downloaded as Excel spreadsheets. STATA/SE (version 16.1; Stata Corp) will be used for statistical analyses. A descriptive analysis will be conducted to summarize the important results. The sociocultural and demographic characteristics of the participants will be summarized. Illness-related questions, such as perceived causes, distress patterns, and help-seeking behaviors, will be presented and compared between different gender and age groups across study areas. The explanatory variables in this study will be social and cultural features of illness experience, meaning and behavior, and questions of awareness and use of the COVID-19 vaccines for prevention. Inferential analysis using regression models will assess the determinants of COVID-19 vaccine acceptance. Narratives of statistically significant factors will be reviewed to better understand their importance.

### Ethical Approval

The study has been approved by the Medical Research Advisory Committee of PNG (MRAC#22.19), the Medical Research Committee of Madang PHA (MAPHAREC 06.22), and the Research and Ethics Committee of Eastern Highlands Province PHA. All participants will provide written informed consent in either English or Tok Pidgin before participating in the study. In the case of illiterate participants, verbal informed consent will be obtained in the presence of a family member or relative. The purpose, procedure, and potential risks of the study will be explained to the participants, and they will be informed that they can withdraw from the study at any time without consequences.

## Results

The project proposal has been reviewed and approved by the Medical Research Advisory Committee of PNG. The permissions required from the provincial health authority to conduct data collection in the selected provinces have been obtained. The research team has recruited participants for in-depth interviews, including key informants in the communities and health facilities. The qualitative data collection started in December 2022, and the preliminary analysis of these data is underway. The insights from the in-depth interviews will be used to further refine the survey instrument by adapting it to the local context. We plan to pretest the survey instrument for validity and proceed with the survey in May 2023. The findings from the interviews and the survey will be disseminated to the participating communities and key stakeholders in a professional dissemination meeting, followed by publication.

## Discussion

### Expected Outcomes

This study’s experiences and findings will contribute to the effective planning and implementation of the COVID-19 vaccine program in PNG. Furthermore, our findings and approach to health social science vaccine research will have implications and potential applications elsewhere for strategic planning of effective action for other vaccines. The following are anticipated specific contributions of the study: (1) identify priorities and approaches for community action based on Melanesian culture to contribute to health system preparedness for control of pandemics; (2) understand the awareness and acceptance of vaccines for COVID-19, indicating the potential value of COVID-19 vaccines in PNG; (3) clarify current views of clinicians and other health professionals concerning their enthusiasm or reluctance to promote vaccine action to control COVID-19; (4) develop and clarify the value of an approach to studying vaccine acceptance in local settings so that planning may consider the relevance of cultural features of health and illness on anticipated and actual vaccine acceptance; (5) clarify features and determinants of COVID-19 vaccine acceptance that can guide policy to ensure that efficacious vaccines are also effective in the context of actual public health action (findings should guide strategic planning to address knowledge gaps and misunderstandings about the benefits and risks of COVID-19 vaccines); and (6) contribute to the National Research Agenda of PNG to strengthen the operation and delivery of the health system and services.

### Potential Impact on Participants

It is possible that participating in the study may influence participants’ views on COVID-19 vaccines. For example, exposure to information about the COVID-19 vaccine or discussions about vaccine hesitancy during data collection may lead participants to change their attitudes or beliefs about the vaccine. To mitigate any unintended consequences and ensure the ethical conduct of the study, we will maintain (1) informed consent, (2) accuracy of information, (3) voluntary participation, and (4) confidentiality. First, all participants will be provided with detailed information about the study and its purpose and will be asked to provide informed consent before participating. This will ensure that participants fully understand the nature of the study and the potential impact it may have on their views. Second, all participants will be provided with accurate and unbiased information about the COVID-19 vaccine, both before and after participating in the study. This will help to ensure that participants have access to the information they need to make informed decisions about the vaccine. Third, participation in the study will be completely voluntary, and participants will be free to withdraw from the study at any time without penalty. This will help to minimize any potential for coercion or undue influence on participants. Fourth, all data collected during the study will be kept confidential and participants’ identities will be protected. This will help to ensure that participants feel comfortable sharing their views and that their privacy is respected.

By taking these steps, we hope to minimize any unintended consequences of the study design on participants’ views on COVID-19 vaccine acceptance and ensure that the study is conducted ethically and with the informed consent of participants.

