## Methods

### Study Design

The research project will use a mixed methods design. The first research component will use a qualitative methodology with an epistemological foundation that is based on constructivism and embraces meaningful reality as it is socially constructed [21]. This design elicits and listens to community members’ accounts of ways culture is a rich source of meaning in the COVID-19 pandemic, their adherence to *niupela pasin*, and their vaccination acceptance. In the context of health, adherence to the new normal is an indicator of the behavior of communities toward their health and is important for understanding these communities. This design will proceed with individual, in-depth, semistructured interviews with community members, community opinion leaders, and church leaders.

The second component, a cross-sectional survey, will use data collected from ethnographic key informant interviews to develop an instrument with open-ended and closed questions. The survey design adapts the WHO immunization and vaccine-related implementation research advisory committee’s vaccine stakeholder framework to assess the awareness, priorities, and practices of community members. This design includes an integrated quantitative and qualitative methods approach, and the data collected will indicate the distribution of key features of vaccine acceptance and demand [22].

The third component, semistructured interviews with health care providers actively involved in either COVID-19 clinical management or public health–related pandemic control activities, will determine vaccine acceptance factors. This component will focus on assessing health care providers’ views on personal vaccine acceptance and their role in facilitating community vaccination.

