### Vaccine Acceptance Survey

A random sampling strategy will be used to select the participants for this survey. We plan to use either the voters’ list or household listings to randomize the sample at an individual level or use village maps to randomize households to select the eligible participants. This will be achieved in collaboration with the provincial health authority (PHA). However, randomization depends on the availability of these resources. Otherwise, a convenience sample will be selected from the urban and rural areas of the selected study sites, stratified by gender (with a 50% distribution) and age group (18-40 years and 41-65 years). Trained research assistants working in 2 teams will conduct the survey, one interviewing and the other responsible for maintaining the data records. Approximately 360 interviews will be conducted (180 in each of the two regions. We calculated the sample size at a 5% margin of error with a 95% confidence level and a 50% response distribution.

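### Giving all participants vaccine information before they are interviewed risks biasing the awareness and acceptance levels that the survey measures

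*Protocol article*

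**What the plan says.** The Potential Impact on Participants section opens by conceding that taking part may influence views: "exposure to information about the COVID-19 vaccine or discussions about vaccine hesitancy during data collection may lead participants to change their attitudes or beliefs". It then lists four safeguards. The first is informed consent based on information about the study. The second, stated separately and with its own purpose of helping people decide about vaccination, is that "all participants will be provided with accurate and unbiased information about the COVID-19 vaccine, both before and after participating in the study". The section closes: "we hope to minimize any unintended consequences of the study design on participants’ views on COVID-19 vaccine acceptance".

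The measurements at issue are set out in Methods:

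- Study Design gives the design, "The second component, a cross-sectional survey, will use data collected from ethnographic key informant interviews", and says the survey is meant "to assess the awareness, priorities, and practices of community members".
- Quantitative Analysis gives the outcome: "Inferential analysis using regression models will assess the determinants of COVID-19 vaccine acceptance". The explanatory variables include "questions of awareness and use of the COVID-19 vaccines for prevention".
- Vaccine Acceptance Survey gives the size, "Approximately 360 interviews will be conducted (180 in each of the two regions", and the planning inputs: a 5% margin of error, 95% confidence and a 50% response distribution.

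Limitations names restricted regional coverage, social desirability and stigma. It does not mention information given before the interview.

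**The concern.** The exposure named as a possible influence on views is also listed as a protection, and half of it is scheduled before the questions are asked. If the information changes what people know or think, their answers describe people who have just been informed by the study team. The communities as they stood before the visit are then not what is measured.

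What is exposed is the absolute level of awareness and of anticipated acceptance. Expected Outcomes says the findings should guide action on knowledge gaps and misunderstandings, and information given first could close some of those gaps before they are recorded. Awareness is also an explanatory variable. If everyone is informed just before being asked, it may vary less between respondents, or may partly reflect recall of what was just said. Since the survey measures each person once and no uninformed group is described, any shift could be neither estimated nor adjusted for.

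**Working it through.** **1. Order of events, from the text.**

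| Step | Source in the article | Content |
|---|---|---|
| Consent | Potential Impact on Participants, first safeguard; Ethical Approval | Study purpose, procedure, risks |
| Vaccine information | Potential Impact on Participants, second safeguard | Promised to all, before participation |
| Single interview | Study Design; Vaccine Acceptance Survey | Awareness, priorities, practices, acceptance |
| Vaccine information again | Potential Impact on Participants, second safeguard | Promised to all, after participation |

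The second row is separate from consent and precedes the only measurement. The fourth row alone would meet the stated purpose of informing participants, without touching the answers.

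**2. The planned precision.** With p = 0.5, d = 0.05 and z = 1.96, n = z²p(1−p)/d² = 3.8415 × 0.25 / 0.0025 = 384.1, so 385. The article says approximately 360, so the stated inputs do not reproduce that figure. At n = 360 the margin is 1.96 × √(0.25/360) = 0.0516, or 5.16 points. This mismatch is a separate matter and does not bear on the present point; 5 points serves here only as a yardstick.

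**3. Illustrative shifts.** The documents give no effect of information on acceptance, so the fractions below are assumptions. Start from 50% acceptance, the planning value. If a fraction f of the non-accepting half changes its answer, measured acceptance rises by f × 50 points:

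- f = 5%: 0.05 × 50 = 2.5 points
- f = 10%: 0.10 × 50 = 5 points
- f = 20%: 0.20 × 50 = 10 points

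If instead the same fraction of the accepting half moves to refusal, the shift has the same size with the opposite sign. Movement in both directions would partly or wholly cancel.

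**4. What such a shift does to a 95% confidence interval at n = 360.** Let b be the shift, p = 0.5 + b and s = √(p(1−p)/360). Coverage of the true 50% is Φ(1.96 − b/s) − Φ(−1.96 − b/s).

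| Assumed shift b | s | b/s | Coverage of the true value |
|---|---|---|---|
| 0 | 0.02635 | 0 | 95% |
| 2.5 points | 0.02632 | 0.95 | 84% |
| 5 points | 0.02622 | 1.91 | 52% |
| 10 points | 0.02582 | 3.87 | 3% |

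Downward shifts give the same coverage, because p(1−p) is symmetric about 0.5. A larger sample does not help: it narrows the interval around the shifted value.

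**5. Comparisons.** The Analysis Plan centres comparison on gender and rural-urban features. If the information shifts both groups by the same number of points, the difference between them is unchanged. It is biased only if the groups respond differently to the information, and the article says nothing on that.

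**The case against.** The strongest reply is that the article never describes a briefing. It gives no content, length or form for the information, and a leaflet or a few lines at consent might satisfy the sentence. The field procedure under In-depth Interviews has the team explain the visit and obtain consent, and Ethical Approval covers purpose, procedure and risks; neither mentions vaccine facts. The sentence may be a loosely worded ethical assurance, and the interviewer script is not shown. This stands as a limit on certainty: the documents support a risk if the sentence is followed, and do not show that answers will be changed. It does not remove the contradiction, because the commitment is explicit, covers all participants and is listed apart from consent.

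A reader might infer more than the text supports:

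- **That acceptance will be overstated.** The information is promised to be balanced, and Research on COVID-19 Vaccine Acceptance reports safety doubts as a frequent reason for refusal. Information on risks could move people either way, or not at all.
- **That awareness will reach a ceiling.** Baseline awareness is not given. The rollout began in May 2021 and the survey is planned for May 2023, so awareness may already be high and the information may add little.
- **That the team would be cueing the answer it wants.** This is conjecture. Limitations plans open-ended questions and probes against social desirability.
- **That all findings are compromised.** Equal exposure does not by itself bias the planned contrasts. Past vaccine use cannot be altered by information given minutes earlier, though its reporting might be. Questions on perceived causes, distress and help-seeking concern the illness and not vaccine facts.

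**Conclusion.** The concern holds as a risk built into a stated procedure. The article identifies vaccine information as a possible influence on views and then schedules it before the only measurement of awareness and anticipated acceptance, without listing this as a limitation. Absolute levels are at risk, and awareness may lose variation or meaning as an explanatory variable. Gender and rural-urban contrasts are not automatically affected.

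Size and direction are unknown. The illustrative 2.5 to 10 points rests on a 50% starting level and on assumed fractions of 5% to 20% changing their answer in one direction; neither fraction nor direction comes from the article. Within that range a shift could equal or exceed the planned margin. The conclusion itself rests on the order of events and needs none of these figures.

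**What to change.** Before the interview, give only neutral consent content: purpose, procedures, risks, voluntariness, and the possibility that taking part may affect one's views. Give the substantive vaccine information once the last answer has been recorded. In the second safeguard, change the timing from before and after participation to after completing the interview, and apply it to the survey and to the in-depth interviews still to be done.

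For interviews already held (qualitative data collection began in December 2022), report whether vaccine information came first, and list it as a limitation if it did.

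The cost is one sentence in the protocol and a change to the interviewer script. There are no added participants or visits, and everyone still receives the information. Ethical Approval names three approving committees. Because the change alters a promised protection, each should be informed or asked to approve, as it requires. The survey was still to start and its instrument was still being refined, so the change can be made before survey data are collected.

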### Limitations

The proposed study design does not include any provinces from the Southern or Islands regions of PNG. We recognize that the generalizability of our study findings will be limited to the Highlands and Coastal regions. However, the Southern and Islands regions can also be categorized as coastal areas. In addition, this study might be subject to social desirability bias. In general, participants will provide responses that they believe are socially acceptable, rather than responding truthfully. To address this potential bias, open-ended questions and follow-up probes will be used to encourage participants to provide detailed and honest responses. However, some participants may still be hesitant to disclose certain information. In addition, the study will be limited by the potential impact of stigma on recruitment and participation. Participants might be hesitant to participate or disclose certain information due to concerns about stigma or judgment. Efforts will be made to address these concerns, including providing a safe and confidential environment for participation, but the impact of stigma on the findings will be considered when interpreting the results.

## Abbreviations

CEPI: Coalition for Epidemic Preparedness Innovations
COVAX: COVID-19 Global Vaccine Access
GAVI: Global Alliance for Vaccine and Immunization
LMICs: low- and middle-income countries
NCC: National Control Centre
NPI: nonpharmaceutical interventions
ODK: Open Data Kit
PHA: provincial health authority
PNG: Papua New Guinea
SAGE: Strategic Advisory Group of Experts
UNICEF: United Nations Children’s Fund
WHO: World Health Organization
